### Study procedure

Once a caregiver agrees to participate, a study team member will schedule a session with them. All sessions will be conducted either online via a video-conferencing platform like Zoom or in-person, based on the caregiver’s preference. After the study team member goes through the informed consent form and obtains the participant’s signed consent, screening will be done using the 4-item version of the Zarit Burden Interview (ZBI) [40]. Caregivers who score 4 and above will be included in the study, while those who score 3 and below will be excluded.

A study team member will assign participants to either the intervention or wait-list control group using block randomisation with a block size of four. An independent statistician not involved in the day-to-day administration of the project will conduct the randomisation by generating a sequence of numbers using the Sealed Envelope online tool on the randomisation website [41]. Allocation concealment is achieved by the ’sealed envelope’ method, in which the envelope contains a random code that must be checked against the randomisation list to determine group information. This is to prevent potential selection bias. Thereafter, the participant will be allocated into a group and complete the baseline assessment. One month later, a study team member will contact the participant to complete the post-assessment. Intervention group participants will also be invited to join a semi-structured interview to share their experience with the app and feedback on areas for improvement. Participants will be disbursed an inconvenience fee through cash or cashless modes of payment on completion of the baseline assessment (SGD25), post-assessment (SGD35), and follow-up interview (SGD30). Please refer to Fig 1 for the schedule of enrolment, intervention, and assessments. The approved study protocol can be found in S2 File.

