## Methods

### Study design

A pilot two-armed randomized control trial (RCT) design will be adopted to test the effectiveness of the *Kampung Care* app (*Kampung Care* is a local expression of a caring community). Sixty eligible caregivers of PWD will be enrolled in the RCT and randomly allocated to either the intervention or control group. No blinding will be used as participants and study team members need to be aware of which group the participant belongs to in order to start the intervention. Participants in the intervention group will use the app for one month, while those in the control group will be on a waiting list for one month. Outcome measures will be assessed at baseline and one-month after the baseline assessment (post-assessment). Thereafter, qualitative interviews will be conducted with participants from the intervention group to gather feedback on their experience with the app and areas for improvement. The Standard Protocol Items: Recommendations for Interventional Trials (SPIRIT) checklist is provided (see S1 File).

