### Sample size

Given that this is a pilot RCT with the primary aim of assessing the feasibility and potential effectiveness of the ’Kampung Care’ mobile intervention, we followed the recommendation from a methodological study that a sample size of 25 per intervention arm is required if the main study is designed with 90% power and two-sided 5% significance for an intervention with a small effect size [39]. No formula or software was used in the calculation. With a 1:1 allocation ratio, the required sample size was determined to be 50. As mobile-based intervention studies tend to have high attrition rates, we doubled our preliminary sample size to 100 to ensure there will be a sufficient sample for analysis. However, following the initial recruitment, we found the attrition rate among our target group to be quite low and thus adjusted our final sample to 60 –with 30 participants randomly allocated to the intervention group and waitlist control group respectively. For the in-depth interview, we intend to recruit up to 20 participants from the intervention group. This is from an experiential perspective. However, the final sample will depend on data saturation–the point at which no new information is being observed and collected to form distinct themes.

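### One fixed block size of four in an unblinded trial leaves an expected third of allocations deducible by staff who know the size and track the sequence

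*Protocol article*

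**What the plan says.** In the protocol article, Study procedure fixes the method: "A study team member will assign participants to either the intervention or wait-list control group using block randomisation with a block size of four". It gives one size and describes neither variation nor strata. The sequence comes from outside the team: "An independent statistician not involved in the day-to-day administration of the project will conduct the randomisation by generating a sequence of numbers". Concealment is by a sealed-envelope method, "in which the envelope contains a random code that must be checked against the randomisation list to determine group information", and the section says that this is meant to prevent selection bias.

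Study design states: "No blinding will be used as participants and study team members need to be aware of which group the participant belongs to". Under Study procedure, a study team member arranges the session and takes consent. Eligibility then turns on the 4-item Zarit Burden Interview, with a score of 4 or more included and 3 or less excluded. The legend to Fig 1 places screening, allocation and baseline assessment in one session, in that order. Under Intervention delivery, a team member telephones intervention participants every week.

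Sample size gives the final number as 60, "with 30 participants randomly allocated to the intervention group and waitlist control group respectively".

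**The concern.** Concealment can fail in two ways: staff can read the next assignment, or they can work it out from earlier ones. Sealed envelopes and an independent sequence guard against the first. A short block of constant size leaves the second open when the people who enrol also see past allocations.

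Here the team knows its own protocol, learns each participant's arm in routine work, and controls when sessions take place. Staff who can deduce the next arm could, deliberately or not, bring a session forward or hold it back, encourage one caregiver more than another, or be more or less generous when a screening score lies between 3 and 4. The arms could then differ at entry in ways related to depressive symptoms, the primary outcome.

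Blinding the final-analysis statistician does not help, because that person acts after enrolment. Adjustment for baseline CES-D is only a partial remedy. It cannot capture unmeasured differences, and the baseline score is collected after allocation in an open session.

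**Working it through.** **Inputs from the protocol article**
- Block size 4, fixed (Study procedure).
- Allocation ratio 1:1 (Sample size).
- Final sample 60, 30 per arm (Sample size).
- Study team unblinded (Study design).

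**Assumptions, not stated in the article**
- Enrolling staff know the block size.
- They follow all earlier allocations in order.
- There is a single list.

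**Step 1: the plan's own figure.** 60 / 4 = 15 complete blocks. Each block gives 2 per arm, so 15 × 2 = 30 per arm, which agrees with the article. The article gives no predictability figure.

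**Step 2: allocations known with certainty.** There are C(4,2) = 6 equally likely blocks: AABB, ABAB, ABBA, BBAA, BABA, BAAB.
- Positions 1 and 2 are never determined.
- Position 3 is determined when the first two match, which is 2 of 6 blocks.
- Position 4 is always determined, which is 6 of 6 blocks.

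Expected number per block = (2 + 6)/6 = 8/6 = 1.33. Share = 1.33/4 = 33.3%. Over 15 blocks, 15 × 8/6 = 20 of 60. Each block contributes 1 or 2 determined allocations, so the possible range is 15 × 1 = 15 to 15 × 2 = 30.

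**Step 3: best-guess accuracy.** The observer always names the arm with more places left in the block, and tosses a coin when they are equal.
- Position 1: 1/2.
- Position 2: 2/3.
- Position 3: (1/3 × 1) + (2/3 × 1/2) = 2/3.
- Position 4: 1.

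Sum = 17/6. Divided by 4 this is 17/24 = 70.8%, against 50% under simple randomisation.

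**Step 4: alternatives.** Fixed, known sizes were enumerated in the same way. For varying sizes, 3,000 trials of 60 were simulated, with each size in the set equally likely. The observer knows the set but not the block boundaries, and updates by Bayes' rule after each allocation.

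| Scheme | Known with certainty | Best guess correct |
|---|---|---|
| Fixed 4 (the plan) | 33.3% | 70.8% |
| Fixed 6, known | 25.0% | 68.3% |
| Fixed 8, known | 20.0% | 66.6% |
| Varying 4, 6 | 5.6% | 69.1% |
| Varying 4, 6, 8 | 2.2% | 67.8% |

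In a trial of 60, 5.6% is about 3 allocations and 2.2% is about 1, against 20 under the plan.

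**Step 5: price in balance.** All sizes are even, so at 60 participants an unfinished block has an even number filled. With sizes 4 and 6 the largest excess is 2 (31:29). With a block of 8 stopped after four of one arm it is 4 (32:28). This takes a list that uses the new sizes from its start, or from the end of a complete block of four.

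**The case against.** **The 33% is conditional.** It requires staff who know the size, know where blocks begin and track the whole sequence. The article does not say that any one enroller does this. It refers to a study team member for scheduling, consent and assignment without saying that it is the same person, and it does not name who scores the screen. That there is one unstratified list is inferred from silence. This objection stands in part: 33% is what an attentive observer could deduce, not an estimate of what happened. The conditions are nevertheless realistic for an unblinded team and a sample of 60.

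**The route to bias is narrow.** Eligibility is a numerical cut-off rather than a judgement, and screening comes before allocation. This is fair, and no effect on CES-D has been quantified. Session timing and encouragement to take part remain in the team's hands, and neither is governed by the cut-off.

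**The remedy gains little in guessing accuracy.** This is correct. Accuracy falls by about 2 to 3 percentage points. What nearly disappears is certainty.

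**Two stronger readings are tempting but not supported.** A reader might infer that looking up the envelope code on the list weakens concealment because whoever does so can see later assignments. The article does not say who holds the list or performs the lookup, and the full protocol (S2 File) is not shown. If an independent person holds the list, a code in place of a group label strengthens concealment. A reader might also infer that publication disclosed the block size to recruiters. Nothing shows that the article was public during recruitment, and the argument does not need it, since the team can know its own protocol.

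**Conclusion.** The point holds for the fixed block size. With one size of four and an unblinded team that schedules and assigns, an expected 33% of allocations (about 20 of 60; range 15 to 30) can be deduced with certainty before enrolment, and best-guess accuracy is 71% against 50%. Both figures rest on staff knowing the block size and tracking one list in order.

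The stated safeguards do not close this route, so the aim of preventing selection bias is only partly met. Whether any bias arises, and how large it would be on CES-D, cannot be determined from the article. The documents do not support a conclusion that the envelope-and-code procedure itself is defective.

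**What to change.** For any allocations still to be made:

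1. The independent statistician issues a new list with randomly varying block sizes, such as 4 and 6, or 4, 6 and 8. The sizes are not disclosed to enrolling staff.
2. Each assignment is revealed only after eligibility and the baseline assessment are complete. At present Study procedure and the Fig 1 legend place baseline after allocation in the same session. The change keeps baseline answers free of knowledge of the arm.

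The cost is a new list, a changed order within the session, any amendment this needs, and a possible imbalance of a few participants if the last block is incomplete. The gain is a fall in certain foreknowledge from 33% to about 2–6%. Best-guess accuracy falls only to about 68–69%, so the change reduces the problem without removing it.

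The Trial status section has recruitment running from December 2022 to the end of March 2024. If allocation is already finished, a new list cannot help. The trial report should then state the fixed block size and the unblinded team, and give the resulting predictability as a limitation.

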**Methods:**

A pilot two-armed randomised controlled trial will be conducted on 60 informal caregivers of PWD recruited via convenience and snowball sampling. Thirty participants will be assigned to the intervention group, while another 30 will be in a waiting-list control group. Questionnaires will be administered at baseline and one month after, with the primary outcome being the difference in the change of depressive symptoms among the two groups.

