**Fig 1 pone.0305729.g001:**
[figure not shown]
SPIRIT figure; schedule of enrolment, intervention, and assessments. *During enrolment, informed consent and eligibility screening will be conducted. Group allocation will be conducted immediately after if the participant meets the screening criteria. Thereafter, baseline assessments will be conducted immediately in the same session as well.

This study will be conducted in accordance with the latest version of the Declaration of Helsinki. Ethical approval for the study protocol was obtained from the National Healthcare Group’s Domain Specific Review Board (DSRB No: 2022/00029) (see S3 and S4 Files). Participation is voluntary and withdrawal from the study is possible at any point in time. Participants may also be asked to stop their participation at any time if they do not follow instructions required to complete the study adequately. All participants will provide written informed consent prior to their participation. Please refer to Fig 2 for the flow of the study procedure.

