### Outcomes

Assessments to examine caregiver outcomes will be conducted at baseline and one month after baseline (post-assessment) for both the intervention and control groups. These will be conducted in English either online via videoconferencing or face-to-face at a location preferred by the participants.

The English version of the following questionnaires will be used in our study:

Centre for Epidemiological Studies-Depression (CES-D) ScaleGeneralized Anxiety Disorder– 7 item scaleZarit Burden InterviewRevised Scale for Caregiving Self-efficacyDementia Knowledge Assessment ScaleCoping Orientation to Problems ExperiencedPositive Aspects of Caregiving ScalePositive Mental Health instrument (short form)

The 20-item Centre for Epidemiological Study Scale (CES-D) will be used to measure the primary outcome–depressive symptoms amongst caregivers [50]. The instrument comprises 20 items, each rated on a 4-point Likert scale from 0 (*rarely or none of the time*) to 3 (*most or almost all the time*). The total score ranges from 0 to 60, with a score of 16 or higher indicating a risk for clinical depression [51]. The CES-D is a widely used scale which has been validated in Singapore [52] and was found to have an internal reliability of 0.91 when used in our previous study [25]. It also demonstrated good validity and reliability in detecting caregiver depression in another local study amongst caregivers of PWD [53]. Please see Table 1 for details on the secondary outcome measures.

**Table 1 pone.0305729.t001:** Measurement of secondary outcomes in the study.

Outcome	Questionnaire	Description
Anxiety	Generalized Anxiety Disorder– 7 item scale (GAD-7)	Each item of the Generalized Anxiety Disorder– 7 item scale (GAD-7) [54] is scored on a 4-point Likert scale from 0 (not at all) to 3 (nearly every day), with scores ranging from 0 to 21. A score of 10 or higher has been recommended as a cut-off point for identifying cases of GAD, while cut points of 5, 10, and 15 can be interpreted as mild, moderate, and severe levels of anxiety respectively [54]. The GAD-7 has been validated amongst the general population in Singapore [55] and used on a sample of local primary caregivers with a high internal consistency of 0.89 [56].

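### Allocation precedes the baseline questionnaires in an unblinded trial, so the baseline CES-D may be answered with the group known, which could bias the change-from-baseline primary comparison

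*Protocol article*

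**What the plan says.** After consent and the 4-item Zarit screen, the Study procedure section of the protocol article states "A study team member will assign participants to either the intervention or wait-list control group using block randomisation with a block size of four". It describes concealment by envelope and then continues: "Thereafter, the participant will be allocated into a group and complete the baseline assessment".

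The note to Fig 1 gives the same order. On allocation, after consent and screening: "Group allocation will be conducted immediately after if the participant meets the screening criteria". On the baseline: "Thereafter, baseline assessments will be conducted immediately in the same session as well".

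On masking, the Study design section says "No blinding will be used as participants and study team members need to be aware of which group the participant belongs to"; the sentence goes on to give starting the intervention as the reason. The Data analysis section blinds only the statistician who does the final analysis.

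On the outcome, the Outcomes section says "The 20-item Centre for Epidemiological Study Scale (CES-D) will be used to measure the primary outcome", and the Abstract defines the endpoint as a contrast of changes: "with the primary outcome being the difference in the change of depressive symptoms among the two groups". The planned analysis is a repeated measures ANOVA over the two time points.

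**The concern.** A baseline is safe from the effects of allocation only if it is recorded before the allocation is known. Here the planned order is the reverse, and the baseline consists of rating scales taken by videoconference or face to face in an unblinded trial. A caregiver who has just learned that she is on the waiting list, or has just been given the app, may rate her symptoms differently from how she would have rated them an hour earlier. The team member conducting the session may also know the group.

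The primary endpoint subtracts this baseline. A reporting difference between arms at baseline that later fades would appear as a difference in change even if the app did nothing. The direction is not predictable. Disappointment in the wait-list arm, or optimism in the app arm, would make the app look worse; the opposite reactions would make it look better. The secondary scales are taken at the same two assessments and are exposed in the same way.

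**Working it through.** No figure in the plan is in dispute, so there is none to reproduce. The check has two parts: the order of steps, and what a baseline shift would do to the estimate.

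**1. Order of steps**

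| Source | Sequence |
|---|---|
| Study procedure text | consent → ZBI-4 screen → allocation → baseline |
| Fig 1 note | consent and screen → allocation → baseline, one session |

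The two agree, so this is the planned sequence and not a slip of wording.

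**2. What protects the baseline**

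- The envelope prevents selection before assignment. It does not act on answers given afterwards.
- Blinding the final-analysis statistician acts after the data are collected.
- No sentence holds back the group until the questionnaires are complete.

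**3. How a shift reaches the estimate**

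With two time points, the group-by-time test of a repeated measures ANOVA is a two-sample test on change scores. Let b be the between-arm shift in reported baseline caused by knowing the group, in SD units, and k the fraction of it still present at one month. Then

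bias in the difference in change = k × b − b = −(1 − k) × b.

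- k = 0 (shift gone): size b.
- k = 0.5: size b/2, so a shift of 0.2 SD leaves 0.1 SD.
- k = 1 (shift fully persistent): zero.

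**4. Illustration of size**

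Inputs from the plan: n = 30 per arm (Sample size); two-sided 0.05 (Data analysis). Assumed, because the plan gives neither: baseline-to-follow-up correlation ρ from 0.5 to 0.8, and net bias B = (1 − k) × b of 0.1 or 0.2 SD. Also assumed: equal SD at both times and no true effect.

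SE = √(2(1 − ρ)) × √(2/30)

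- ρ = 0.5: 1.000 × 0.258 = 0.258
- ρ = 0.8: 0.632 × 0.258 = 0.163

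Rejection rate = Φ(−1.96 − B/SE) + 1 − Φ(1.96 − B/SE)

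| Net bias B | ρ = 0.5 | ρ = 0.8 |
|---|---|---|
| 0 | 5.0% | 5.0% |
| 0.1 SD | 6.7% | 9.4% |
| 0.2 SD | 12.1% | 23.2% |

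A noncentral t calculation at 0.2 SD gives 11.9% and 22.6%, so the normal approximation is adequate.

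**5. Would baseline adjustment solve it?**

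No. If the shift has gone by one month (k = 0), ANCOVA carries ρ × b in place of b. For b = 0.2 SD that is 0.10 SD at ρ = 0.5 and 0.16 SD at ρ = 0.8, with error rates of 7.3% and 17.8%. The bias is smaller but not removed.

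**6. After re-ordering**

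If the baseline is complete before the group is revealed, b = 0 from this source and the 5% level is undisturbed. Sample size and alpha do not change.

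**The case against.** The strongest counter-argument is that the documents fix the order of allocation and baseline but not the moment of disclosure. Being allocated is not the same as being told, and the reason given for not blinding is to start the intervention, which comes after baseline. The figures and the full approved protocol are not shown and might settle the timing. This stands: a reader might infer that caregivers definitely know their group when they answer, and the text supports only that they may. It does not remove the point, because nothing shown withholds the group and starting the intervention does not require allocation before baseline.

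A reader might also infer that any baseline shift passes in full into the primary estimate. That holds only if the shift has vanished by one month. Both arms stay unblinded, so some persistence is plausible, and the change score would then carry less.

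The shift itself is assumed. The CES-D items rate how often symptoms occur, which is less open to a passing reaction than a rating of current mood. The wait is one month and the app is then offered. The plan contains nothing to show that 0.1 or 0.2 SD is realistic.

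Two further inferences go too far. One is that caregivers will leave on hearing they are wait-listed and so have no baseline: the baseline follows at once in the same session, its completion is paid (SGD25), and the Sample size section reports low attrition. The other is that randomisation no longer balances the arms: concealed allocation still balances true depressive status in expectation, and only the reported scores could differ.

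Finally, this is a pilot with feasibility among its aims, so an inflated error rate matters less than in a confirmatory trial. That lowers the priority. It does not excuse the order, because the plan also tests effectiveness at a two-sided 5% level.

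**Conclusion.** The point holds in a limited form. The planned order leaves the baseline CES-D open to reporting bias in an unblinded trial, and the primary comparison depends on that baseline. The documents show that such bias is possible; they do not show that it occurs, how large it is or which way it runs. Its size in the change score is (1 − k) × b, anywhere from the whole shift to nothing. The error rates of about 7% to 9% and 12% to 23% are illustrations that rest on assumed net biases of 0.1 and 0.2 SD and assumed correlations of 0.5 to 0.8. Confidence is high on the order of steps and moderate on disclosure before baseline, which is inferred. Priority: should be fixed, given the pilot aim and the very low cost.

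**What to change.** 1. In the Study procedure text and the Fig 1 note, set the order as consent, ZBI-4 screen, all baseline questionnaires, then opening of the envelope and the check against the list, all in the same session. This swaps two steps and needs a short amendment. It adds no visit, staff or participants.

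2. Recruitment began in December 2022 and runs to the end of March 2024, so some caregivers will have followed the current order. Record which order each participant followed and report that the baseline was taken after allocation for those concerned. Without that record, a mid-trial change would mix two kinds of baseline that could not be told apart.

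3. Add a sensitivity analysis of the one-month CES-D by arm that does not use the post-allocation baseline. It may be adjusted for the ZBI-4 screening score, which is collected before allocation. That score measures burden, not depression, and is truncated at 4 or more by eligibility, so it may recover little precision. Unadjusted, the SE is √(2/30) = 0.258 SD. That equals the change-score SE at ρ = 0.5 and exceeds the 0.163 SD at ρ = 0.8. This analysis removes the baseline shift but still carries any part that persists to one month (k × b), so it should be read beside the primary result and not in place of it. The cost is one extra model.
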